### Collecting Data Using SmartHealth Technologies

KAPM’s SmartHealth technologies (SymptoMaster and Medintel) will be used to capture early symptoms of COPD and signs of COPD exacerbations and comorbidities. Our proprietary expert technology called SymptoMaster [16] will help patients establish the probable causes of the symptoms of diseases without assistance from a health care professional. Using a computer, mobile phone, or tablet, a patient inputs their symptoms into the system, which produces the most likely preliminary diagnosis. After receiving the diagnosis, a patient can refer to Medintel [17], an online library that contains information about 1000 common diseases, their causes, symptoms, ways to prevent them, and treat them. These technologies allow a patient to make an informed decision on whether they should seek immediate medical assistance by calling an ambulance or consult a doctor on their next routine visit. SmartHealth technologies facilitate monitoring patients’ conditions by clinical investigators.

### Computer-Assisted Personal Interviewing

KAPM has developed an electronic data capture system in the form of its proprietary computer-assisted personal interviewing app. The app is available for tablet personal computers and will be modified to be implemented in the cohort study to collect, store, and transmit data related to a personal survey interview. The questionnaire will be designed to collect data on possible COPD risk factors including history of smoking, current smoking, level of smoking exposure (in pack-year), passive smoking, occupational and environmental hazards, including dusts, chemicals, and indoor fuel pollution. The questionnaire will contain covariates: age, gender, ethnicity, education, occupation, and self-reported morbidity. It will also include questions to address COPD exacerbations and to record the use of combustible cigarettes, iQOS with HeatSticks, electronic cigarettes, and other alternatives, as well as iQOS switch date.

### Statistical Analysis and Data Management Plan

Appropriate descriptive statistics will be used to summarize required study elements overall and by cohort (eg, proportion, mean, standard error, median, and interquartile ranges). Exploratory graphical analysis will be done preliminary to numerical analysis. Histograms, two-dimensional scatterplots of raw data, will provide information on the univariate and bivariate distributions of the variables focusing on distribution of variables, relation between the variables, whether it is linear or nonlinear, etc. In addition, preliminary graphs will screen raw data by highlighting obvious data errors. Spaghetti plots, scatterplots of dependent variable scores versus the time variable with a separate line for each person, will explore likely models, especially whether effects are linear or not.

Generalized estimating equations (GEE) and GLMM will be used to assess the effect of exposure on outcome variables. Both GEE and GLMM are used to account for within-person correlation of observations due to repeated measures. GEE uncovers the population average effect of a covariate, whereas GLMM estimates the individual specific effect. For binary confirmatory outcomes, CAT score ≥10, and inability to walk 450 meters on the 6MWT, the logit transformation will be utilized as the model link function. To model the annual exacerbation rate (count data), we will use the logarithm transformation and the Poisson or quasi-Poisson distribution depending on mean-variance relationship.

Presence of the statistically significant “time by group” interaction coefficient in GEE/GLMM will be our focus. It will demonstrate that the primary outcomes in two cohorts will have been changed significantly and provide statistical evidence for the harm reduction hypotheses.

To adjust for confounders, we will examine distributions of all covariates in the exposed and control group and will use Cohen effect sizes [26] to identify whether participants’ characteristics are different between groups at baseline. The impact of a potential confounder will be confirmed on whether the adjustment for the confounding variable changes the estimate of association.

We will apply a three‐stage reporting framework [27]. Model 1 will report the crude analysis (without any adjustments for confounders), Model 2 will report the semi‐adjusted analysis (including the following a priori defined covariates of gender, age, number of pack-year at base-line), and Model 3 will present the fully adjusted model (including all the covariates as in Model 2 plus those covariates that have discrepancies across two cohorts and change the estimate of association). The matching variables can be ignored in the model if we have exactly two controls for each participant in the iQOS cohort. Because of dropouts and other reasons, that will be impossible to achieve. There will be some confounder effect remaining, which means we have to include matching variables in the analysis. Model diagnostic plots will be generated to test model assumptions, for example, normality of deviance residuals.

We will also use two methods of propensity score analysis (PSA)—stratification on the propensity score and inverse probability weighting using the propensity score [28]—to adjust for confounders that may vary in study groups.

For missing data analysis, we will use missing at random assumptions. Missing values will be handled by multiple multivariate imputation in R. We will analyze five copies of the data, each with missing values imputed, in the GEE/GLMM multivariate analysis. The estimates of association will then be averaged according to Rubin’s rule [29] to produce a single mean estimate and adjusted standard errors.

To address dual usage, switching, and quitting, we will use several methods. First, we will implement the intention-to-treatment strategy, that is, we will adjust only for baseline confounders and evaluate the exposure effect as if all study participants remain under the exposures at the baseline until end of follow‐up. Second, we will evaluate the exposure effect censoring switchers and quitters from the analysis. Third, particularly for dual usage, we will model two exposures, iQOS and conventional cigarette usage, as weighted sums of doses calculated in pack-years. Weights will depend on the importance of the different periods, where the closest period will have the highest weight.

Analysis will be done using R [19]. The Bonferroni correction of the significance level will be applied to account for three confirmatory hypotheses being tested in the study, so an alpha <.017 (0.05/3) will be considered significant.

Sensitivity analysis will be performed to assess consistency of the effect estimate by testing variations in underlying assumptions. First, we will assess potential biases due to unmeasured confounders or how strong should be an unmeasured confounder to explain the magnitude of the effect estimate. Second, we will consider the use of more than one cohort definition to ensure that the effect estimate is robust to the assumptions behind these definitions. For example, we will use a different cut-off for predominant use of iQOS with HeatSticks (>50%, >60%, >70%, >80%, >90%, 100%) based on averaging iQOS percentage use over time beginning from baseline. Third, there are several alternative statistical analysis approaches to evaluate the effect estimate. We will explore whether the choice of statistical method (GEE/GLMM/PSA) will influence the effect estimate. Finally, we will search how redefining the threshold (ie, different cut-off points for binary outcomes, CAT, and 6MWT) changes the effect estimate.

All study data will be stored at the Information Technology Unit of КАPM. Data will be entered through a Web-accessible system. The questionnaire will be designed as an HTML Web form and will be placed on the server so that it can be loaded and displayed through the client browser at the time of connection. Data analysis will be done only in aggregate. All data will be used for research purposes only, and no participant will be identified when the data are analyzed, presented, or published. No individually identifiable information will be published. The Ethics Committee of KAPM approved this study on December 5, 2017.

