### Study Procedures

#### Recruitment

We will select 800 current smokers and 400 users of iQOS with HeatStick based on the inclusion criteria. The recruitment strategy for smokers of combustible cigarettes and participants who use iQOS with HeatStick includes word-of-mouth communication to friends and spouses of individuals who participated in the cross-sectional study, advertisements, social media engagement (ie, Facebook, Instagram, WhatsApp chats), and outreach to community groups. In addition, we will recruit users of iQOS with HeatSticks at iQOS stores in Almaty, Kazakhstan.

To achieve comparability of comparison groups at baseline, the matched-pair cohort study design will be implemented, where a pair contains one iQOS with HeatSticks user and two conventional cigarette users. The following variables will be utilized for matching: gender, age (±3 years), education (as a proxy for socioeconomic status), and number of pack-year (±5 pack-years) as the baseline exposure level (number of pack-year).

Once potential participants who meet inclusion criteria are identified, they will undergo further medical assessment at the KAPM COPD Center to test for exclusion criteria and to start baseline comprehensive assessment.

The study will include (1) baseline comprehensive assessment at outset of the study during the enrollment period, which is expected to last for about 6 months (4^th^quarter of 2017 to 1^st^-3^rd^quarters of 2018); (2) annual comprehensive assessments at 2^nd^-4^th^quarters of 2018-2022; (3) periodic prospective case finding and exacerbation history assessment on quarterly basis (every 3 months), semiannual, and annual basis; and (4) continuous COPD case-finding activities based on patient self-assessment and professional clinical assessment during periodic visits to KAPM dedicated primary care unit.

**Table 1 table1:** Sample size calculations.

Primary confirmatory variable	Estimated value of outcome variable in exposure group	Estimated value of outcome variable in control group	Sample size exposed/ nonexposed	Adjusting sample size for anticipated dropouts
Symptomatic smokers defined by CAT ≥10	17%	42.8%	23/46	31/62
6MWT <450 m	11%	16.7%	260/520	347/694
Annual exacerbation rate	0.05	0.1	255/510	340/680

Baseline comprehensive assessment at outset of the study (4^th^quarter of 2017) and annual assessments (4^th^quarters of 2018-2020) will include the following:

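### Models 2 and 3 name no covariate-by-time terms, so for measured factors that are unbalanced between cohorts and affect the rate of change, the decisive time-by-group coefficient would stay near its crude value

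*Protocol article*

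**What the plan says.** All of this is in the protocol article, under Statistical Analysis and Data Management Plan unless noted.

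- **Decisive quantity.** The time-by-group "interaction coefficient in GEE/GLMM will be our focus", and a significant result is to "provide statistical evidence for the harm reduction hypotheses". The sample size section assumes the same kind of effect: associations that start at 1 and grow steadily to their final-visit values.
- **Adjustment.** Model 1 is crude. Model 2 is described as "including the following a priori defined covariates of gender, age, number of pack-year at base-line". Model 3 takes the Model 2 set "plus those covariates that have discrepancies across two cohorts and change the estimate of association". The only interaction named in the section is time by group.
- **Matching.** Recruitment matches one iQOS user to two cigarette smokers on "gender, age (±3 years), education (as a proxy for socioeconomic status), and number of pack-year (±5 pack-years"). The plan accepts that exact 1:2 sets will not survive: "There will be some confounder effect remaining, which means we have to include matching variables in the analysis". Education is a matching variable but is not in the Model 2 list.
- **Other adjustment.** The plan adds "stratification on the propensity score and inverse probability weighting using the propensity score". The sensitivity analyses compare GEE, GLMM and propensity-score results and assess unmeasured confounding.

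**The concern.** A baseline covariate entered by itself explains why some people have more symptoms at every visit. It does not explain why their symptoms worsen faster. If a factor speeds up decline and is less common among iQOS users, the cohorts diverge over time with no product effect, and that divergence falls into the time-by-group coefficient.

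Three things are at stake.

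1. Confounding of trend could produce a significant interaction that is read as harm reduction, or could mask a true one.
2. Model 3 keeps a covariate only if it changes the estimate. A factor that confounds the trend barely moves the time-by-group coefficient when entered alone, so it may be screened out.
3. Close agreement between Models 1, 2 and 3 would look like robustness to confounding, although little adjustment of the tested quantity had taken place.

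Imbalance is plausible. The questionnaire covers occupational and environmental hazards, passive smoking, indoor fuel pollution and self-reported morbidity, none of which is matched. iQOS users are also recruited at iQOS stores, a source the control cohort does not share.

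**Working it through.** The plan prints no figure for this point. The only figure of its own used here is the significance level: 0.05/3 = 0.0167, which it rounds to .017.

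**Why a main effect does not help.** Write the linear predictor as b0 + b1·t + b2·G + b3·G·t + c·C + d·C·t, with G the cohort, t time, C the covariate, and b3 = 0. If C·t is left out, and the cohorts differ by Δ in the mean of C, the G·t coefficient picks up roughly d × Δ. Entering C alone absorbs c·C but not d·C·t.

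**Simulation A.** From the documents: 400 and 800 participants, 10% annual dropout, test level .017, and control values of 42.8%, 16.7% and 0.1 per year, used here as starting values. Assumed: visits at years 0 to 5; one covariate 0.5 SD lower in the iQOS cohort; a level effect of 0.5 per SD; a slope effect of 0.5 log-odds (log-rate for exacerbations) per SD over 5 years; person-level SD 1.5 on the logit scale and 0.8 on the log scale. Analysis: marginal logistic or Poisson model, working independence, robust standard errors, 2,500 replicates. The true time-by-group effect is zero.

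The product rule gives 0.5 × (-0.5) = -0.25 over 5 years, and exp(-0.25) = 0.78. Each cell shows crude / main effect / with covariate-by-time:

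| Outcome, imbalance | 5-year ratio | False positives |
|---|---|---|
| CAT ≥10, 0.5 SD | 0.86 / 0.85 / 1.00 | 8.7% / 8.9% / 1.9% |
| 6MWT <450 m, 0.5 SD | 0.85 / 0.84 / 1.00 | 5.8% / 5.8% / 1.4% |
| Exacerbations, 0.5 SD | 0.77 / 0.77 / 1.00 | 6.2% / 6.6% / 1.8% |
| CAT ≥10, 0.3 SD | not shown | 3.7% / 3.7% / 2.0% |
| CAT ≥10, 0.2 SD | not shown | 2.3% / 2.4% / 1.4% |

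The exacerbation ratio matches the product rule. The logistic ratios lie closer to 1 because marginal logistic coefficients shrink when people vary. For CAT at 0.5 SD the log-scale estimates are -0.154, -0.164 and -0.003. Without dropout they are -0.152, -0.161 and +0.001.

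**Simulation B.** Logistic GEE, 400 and 800 participants, baseline plus four annual visits (the assessments listed in Table 3), two-sided 0.05/3, 600 replicates. Assumed: binary confounder, level effect 0.5 log-odds, random-intercept SD 1, no dropout. The true effect is again zero. Estimates are per year; each cell shows crude / main effect / with covariate-by-time / inverse probability weighting:

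| Confounder, iQOS vs control | Slope per year | d × Δ | Time-by-group estimate | False positives |
|---|---|---|---|---|
| 30% vs 50% | 0.15 | -0.030 | -0.022 / -0.023 / 0.002 / 0.002 | 4.0% / 4.3% / 1.2% / 1.2% |
| 20% vs 50% | 0.15 | -0.045 | -0.037 / -0.038 / 0.000 / 0.000 | 9.0% / 9.5% / 1.0% / 1.7% |
| 20% vs 50% | 0.30 | -0.090 | -0.069 / -0.074 / 0.000 / 0.000 | 34% / 37% / 0.8% / 0.8% |
| 30% vs 30% | 0.15 | 0 | 0.002 in all four | 1.7% to 1.8% |
| 30% vs 50% | 0 | 0 | 0.000 in all four | 1.0% to 1.7% |

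Monte Carlo standard errors are √(p(1-p)/R). At 2.4% with 2,500 replicates this is 0.3 points; at 4.3% with 600 replicates it is 0.8 points.

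**Effect on the selection rule.** In Simulation B, entering the confounder alone moved the estimate by about 3-7% (for example 0.0738/0.0693 = 1.065), and away from zero. Entering it with its product with time removed essentially all of the bias. The plan states no threshold for a change in the estimate, but a shift of that size would be easy to pass over.

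**The case against.** **The form of the covariates is not stated.** The article names covariates, gives no equation, and neither says main effects nor rules out products with time. It also condenses a fuller plan. This stands: a reader might infer that the protocol fixes main-effect adjustment only, and the text does not say so. What it does fix is the decisive coefficient, the make-up of the three models, and a selection rule tied to an estimate of association that is never identified as that coefficient. A statistician following it literally would most naturally add main effects.

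**Weighting is planned and works.** In Simulation B, inverse probability weighting removed the bias with no covariate-by-time term. So a reader who concludes that the harm-reduction question goes essentially unadjusted would be wrong, and the planned comparison of methods could expose a discrepancy. But weighting is an added method, the decisive coefficient is placed in GEE/GLMM, and no rule says which result governs if they differ. Propensity-score stratification reaches the coefficient only if slopes are compared within strata, which is not stated.

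**The Model 2 covariates are matched.** Gender, age and pack-years should be near balance at baseline, and a balanced covariate gave no inflation. It is therefore too broad to say that anything driving the rate of change passes into the test: the factor must also be unbalanced. Dropout can bring imbalance back, but neither simulation modelled dropout that depends on the covariate.

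**The sizes are assumed.** Neither the imbalances nor the slope effects come from the documents. The simulations fitted marginal models; the GLMM was not simulated, although its linear predictor has the same structure.

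**Conclusion.** The point holds in a limited form. As described, Models 2 and 3 would leave the confirmatory coefficient close to its crude value for a measured covariate that meets two conditions: it differs between cohorts and it affects the rate of change. If either condition fails, there is no bias. Unmatched factors carry most of the risk.

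The direction follows from the structure of the model; the size does not follow from the documents. With a slope effect of 0.5 log-odds per SD over 5 years, the false-positive rate for CAT ≥10 under main-effect adjustment runs from 2.4% at 0.2 SD imbalance, a small excess over the nominal 1.7%, to 8.9% at 0.5 SD. Stronger assumed inputs in Simulation B gave up to 37%, an extreme case rather than an expectation.

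The same structure weakens the Model 3 selection rule and means that agreement across Models 1 to 3 would not show robustness. Since the plan itself concludes that remaining confounding is a reason "which means we have to include matching variables in the analysis", their inclusion should be in a form that reaches the tested coefficient.

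**What to change.** - In Models 2 and 3, enter the matching variables (education included) and each candidate or retained confounder together with its product with time.
- State that the change-in-estimate rule applies to the time-by-group coefficient, judged after both terms are added.
- In the propensity-score stratification, estimate time-by-group within strata and pool.
- Report the inverse-probability-weighted time-by-group estimate beside Model 3.
- State that Model 1 is unadjusted for confounding of the trend, and that agreement between models is informative only once the product terms are in.

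The cost is wording and a few model terms, with no new data. In Simulation A the standard error of the focal coefficient rose by about 1-3%; for CAT at 0.5 SD it went from 0.162 to 0.166 (0.166/0.162 = 1.025).

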### Sample Size Calculation

Based on the results of the cross-sectional study, we demonstrated that smoking cessation alleviates activity limitations and airway disease caused by smoking of combustible cigarettes. This is evidenced by the prevalence of a CAT score of ≥10 among those who stopped smoking during the past 1-5 years at 17% compared to 42.8% among current smokers, and reduced inability to walk 450 meters within 6 minutes on 6MWT (11% compared to 16.7% among current smokers).

We hypothesize that switching from combustible cigarettes to iQOS with HeatSticks may reduce the risk of respiratory exacerbation and other COPD manifestations, somewhat similar to the effects of smoking cessation observed in the cross-sectional study.

In the cross-sectional study, duration of smoking abstinence in the second (ex-smoker) study group varied from 1-5 years. This is comparable with the length of the cohort study (5 years) that we propose. Therefore, we can use estimates of the outcome variables derived from the cross-sectional study to calculate required sample sizes that can identify statistically significant differences.

We suggest implementing a matched-pair cohort study design where a pair contains one iQOS with HeatSticks user and two conventional cigarette users matched by gender, age, education, and baseline exposure level (number of pack-year). By selecting this study design, we take into account the limited number of iQOS users from which the first (exposure) cohort is planned to be recruited.

To perform sample size calculation, we will assume that the associations we observed in the cross-sectional study between primary confirmatory outcomes and the smoking status (ex-smokers vs current combustible cigarette smokers) will be the same for iQOS users as compared to combustible cigarette smokers at the final visit after 5 years:

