At the final visit, the odds ratio of association between the exposure and CAT score of ≥10 will equal 0.27 and a CAT ≥10 prevalence will be 42.8% in the control group.At the final visit, odds ratio of association between the exposure and inability to walk 450 meters on the 6MWT will equal 0.62 and a 6MWT <450 meters prevalence will be 16.7% in the control group.At the final visit, rate ratio of association between the exposure and exacerbations will equal 0.5 and annual exacerbation rate will be 0.1 in the control group based on conservative estimations from Woodruff et al [10]. We also assume that these associations will increase steadily from 1 to the above-indicated values. Sample size calculations for three primary confirmatory outcomes have been performed by simulations and the frequentist method based on the power and level of significance of a test. For each primary confirmatory outcome, we have generated data from the distribution assumed for the combustible cigarette smokers and the distribution for the iQOS with HeatSticks smokers (based on our assumptions of how their changes in respiratory symptoms prevalence, proportions of participants who walk less than 450 meters, and annual exacerbation rate might be different if switched from combustible cigarettes to iQOS with HeatSticks). We have used R [19] for simulations (1000 simulations per each primary confirmatory outcome variable) and fitting a generalized linear mixed-effects model (GLMM) on simulated data (function “glmer” in the package “lme4”). For sample size calculation, we have used a power value of 80%, two-sided significance level (alpha) 1.7% that accounts for multiple hypotheses testing, and 1:2 ratio for sample sizes of the experimental and control cohorts.

Then, we have adjusted the sample size for anticipated proportion of dropouts (taking into consideration a 10% annual dropout rate and the fact that already collected data relating to any participant who stops the study early will be analyzed). Sample size calculations are presented in Table 1.

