### Limitations

This study is observational. Despite the fact that we have collected an extensive set of data on possible confounders, unmeasured confounding variables may exist. The study cannot produce definitive proof of a cause-effect relationship between the exposures and health outcomes, as with any observational medical research. Participants may leave the study for different reasons, which can compromise the validity of the study, particularly if the cohort dropout rates are different or the participants who remain in the study are different from those who drop out.

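### With 34% to 41% of last-visit outcomes expected to be missing, the plan fixes five imputations under missing at random, and none of its listed sensitivity analyses varies that assumption

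*Protocol article*

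**What the plan says.** The Statistical Analysis and Data Management Plan section of the protocol article makes two firm choices on missing data: "For missing data analysis, we will use missing at random assumptions" and "We will analyze five copies of the data, each with missing values imputed". The results are combined by Rubin's rule. The quantity of interest is the time-by-group interaction in GEE or GLMM, tested at 0.017 for each of three outcomes.

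The Sample Size Calculation section sizes the study "taking into consideration a 10% annual dropout rate", and adds that "already collected data relating to any participant who stops the study early will be analyzed". The assumed effects apply to "smokers at the final visit after 5 years". In Table 3 the last scheduled CAT and 6MWT fall in Year 5 Q1, the fourth annual follow-up.

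The sensitivity paragraph lists four analyses: unmeasured confounding, cohort definition, choice of statistical method, and outcome cut-offs. The Limitations section says that dropout can compromise validity, "particularly if the cohort dropout rates are different" or if those who stay differ from those who leave.

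**The concern.** Two things are at stake, and they differ in kind.

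The first is the number of imputations. With few copies, the between-imputation variance is poorly estimated, Rubin's degrees of freedom are low, and the critical t value rises. The Bonferroni level makes this worse because the cut-off lies far out in the tail. Near the 0.017 boundary, the result then depends partly on the random seed.

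The second is the assumption itself. Missing at random cannot be checked from the observed data. With a third or more of the last-visit outcomes imputed, a reader will want to know how far dropouts would have to depart from it before a conclusion changes. The sensitivity paragraph is introduced as a test of underlying assumptions, but this one is not on its list.

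**Working it through.** **The plan's own dropout figure.** Table 1 inflates 23/46, 260/520 and 255/510 to 31/62, 347/694 and 340/680. Dividing by 1 − 0.25 and rounding up reproduces all of these, for example 260/0.75 = 346.7 → 347 and 255/0.75 = 340. So 25% is an average loss over visits. A linear loss of 10 points a year averages 25% over visits 0 to 5 (0, 10, … 50%). This does not conflict with a larger loss at the last visit.

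**Loss at the last visit.** Compounding 10% a year:
- four years: 1 − 0.9^4 = 34.4%, leaving about 262 of 400 and 525 of 800
- five years: 1 − 0.9^5 = 41.0%, leaving about 236 of 400 and 472 of 800

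**Fraction of missing information (FMI).** The article gives none. I assumed a linear slope over annual visits, a Gaussian approximation, exchangeable within-person correlation of 0.2 to 0.7, equal 10% annual dropout in both cohorts, and data before dropout retained. FMI is 1 minus the ratio of the slope variance with complete data to that with dropout. This gives 0.23 to 0.27 with four annual follow-ups and 0.28 to 0.32 with five.

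**Interval width.** Relative to unlimited imputations, width = √(1 + FMI/m) × t / 2.394. Here 2.394 is the normal quantile for two-sided 0.05/3, and t has (m − 1)/FMI² degrees of freedom.
- m = 5, FMI 0.23: 1.0227 × 2.448 / 2.394 = 1.046
- m = 5, FMI 0.32: 1.0315 × 2.501 / 2.394 = 1.078
- m = 50: 1.004 and 1.007

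If the degrees of freedom instead use λ = (1 + 1/m)·FMI/(1 + FMI/m), the m = 5 figures become 1.054 and 1.091. Most of the widening comes from the t quantile. The relative efficiency of the estimate, 1/(1 + FMI/5), is still 0.956 to 0.940.

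In simulation, a test with exactly 80% power at unlimited m falls to about 74% with m = 5 and FMI 0.25, and stays at about 80% with m = 50.

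**Seed dependence.** For fixed data, the pooled estimate varies between seeds with a standard deviation of √(FMI/m) standard errors. That is 0.21 to 0.25 at m = 5 and 0.07 to 0.08 at m = 50. A one-standard-deviation change of 0.25 takes a z of 2.39 to 2.14 or 2.64, or p to about 0.032 or 0.008 (normal approximation, before counting the variation in the standard error).

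**Departure from missing at random (illustration).** Inputs are Table 1: 6MWT 11% against 16.7%, CAT 17% against 42.8%. Let d be the proportion missing and k the factor on the dropouts' odds. Exposed prevalence = (1 − d)·p + d·p_k, where p_k has odds k·p/(1 − p). For 6MWT with d = 0.41 and k = 2: odds 0.11/0.89 = 0.1236, doubled 0.2472, so p_k = 0.198. The mixture is 0.59 × 0.11 + 0.41 × 0.198 = 0.146, with odds 0.171. Against control odds 0.167/0.833 = 0.2005, the OR is 0.85.

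| Outcome (OR with no shift) | k | Exposed only, d = 34% | Exposed only, d = 41% | Both cohorts |
|---|---|---|---|---|
| 6MWT (0.62) | 2 | 0.81 | 0.85 | 0.62 |
| 6MWT (0.62) | 3 | 0.99 | 1.06 | 0.63 |
| CAT (0.27) | 2 | 0.36 | 0.38 | 0.28 |
| CAT (0.27) | 3 | 0.43 | 0.46 | 0.30 |

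**The case against.** **Limitations paragraph.** A reader might infer that the plan itself doubts missing at random, or contradicts itself. The text does not support that. It speaks of dropout rates that differ between cohorts and of remainers who differ from leavers. It does not say that dropout depends on unobserved outcomes. Both conditions can hold under missing at random if the differences run through cohort, measured covariates or earlier outcomes. The paragraph gives a reason to examine the assumption, not evidence against it.

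**Size of the imputation loss.** A reader might take the 41% as the FMI, which would give a widening of 12% to 14% at m = 5. But the test is on the time-by-group coefficient and earlier visits are kept, so the lower range fits better. At FMI 0.1 to 0.2 the widening is only about 1% to 4%. Nor is a wider t interval the same as discarding that share of the sample.

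**One-sided shift.** The movement in the 6MWT odds ratio comes almost entirely from assuming that only exposed dropouts depart from missing at random. Nothing in the article shows such asymmetry, and a reader should not infer that dropout will erase the 6MWT effect. The illustration also concerns a single visit; the interaction across all visits would move less. It does not cover exacerbation rate.

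**Omission in a condensed article.** A sensitivity analysis outside missing at random could stand in an analysis plan that is not shown, and the article does not say its assumption excludes others. This has force. Still, the article states the assumption and the number of copies outright, and its enumerated list runs from first to last without varying the assumption. The listed items do not substitute: GEE and GLMM receive the same imputed data, propensity methods address confounding, and censoring switchers and quitters concerns changes in exposure.

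**Conclusion.** The point stands at moderate size. Five imputations are too few for this amount of dropout at a 0.017 threshold. The cost is an interval about 5% to 8% wider (up to 9% with the alternative degrees of freedom) and p values near the boundary that shift with the seed. It does not bias the estimate. These figures rest on an assumed FMI of 0.23 to 0.32.

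The untested assumption is the weightier half. Under a cohort-specific departure, the last-visit 6MWT effect could shrink to nothing, while the CAT effect would remain at an OR of at most about 0.46. Under an equal departure in both cohorts, neither moves much. The figures show how sensitive the result could be; they do not predict what will happen. The 34% to 41% loss is likewise the plan's own planning rate carried forward, not an observed figure.

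**What to change.** In the Statistical Analysis and Data Management Plan section, replace five imputations with at least 50.

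Add to the sensitivity paragraph a delta-adjusted (pattern-mixture) rerun of the same imputation. Multiply the odds of the outcome for dropouts by factors from 1 to 3, first in the exposed cohort only and then in both. Report the factor at which significance at 0.017 is lost. Fix the grid of factors before outcome data are examined.

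The cost is computing time, a few lines of code and a little extra reporting. Recruitment, visits and procedures do not change.
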